**Version History of Statistical Analysis Plan**

| Version Number | Date       | Changes         | Reason for Revision |
|----------------|------------|-----------------|---------------------|
| 1.0            | 2025-02-25 | Initial Version | N/A                 |

## Abbreviations

| Abbreviation | Annotation                                            |
|--------------|-------------------------------------------------------|
| ALP          | Alkaline Phosphatase                                  |
| ALT          | Alanine Aminotransferase                              |
| ANCOVA       | Analysis of Covariance                                |
| AST          | Aspartate Aminotransferase                            |
| ATC          | Anatomical Therapeutic Chemical Classification System |
| BMI          | Body Mass Index                                       |
| CDE          | Center for Drug Evaluation                            |
| CI           | Confidence Interval                                   |
| CMH          | Cochran-Mantel-Haenszel Test                          |
| Cr           | Creatinine                                            |
| CRF          | Case Report Form                                      |
| CS           | Clinically Significant                                |
| eCRF         | Electronic Case Report Form                           |
| FAS          | Full Analysis Set                                     |
| Fisher       | Fisher's Exact Probability Test                       |
| GAD-7        | Generalized Anxiety Disorder-7                        |
| HGB          | Hemoglobin                                            |
| LOCF         | Last Observation Carried Forward                      |
| ITT          | Intention-to-treat Analysis                           |
| Max          | Maximum                                               |
| Mean         | Mean                                                  |
| MedDRA       | Medical Dictionary for Regulatory Activities          |
| Median       | Median                                                |
| Min          | Minimum                                               |
| MMRM         | Mixed-effect Models for Repeated Measures             |
| NCS          | Not Clinically Significant                            |
| NMPA         | National Medical Products Administration              |
| PHQ-9        | Patient Health Questionnaire-9                        |
| PLT          | Platelets                                             |
| PPS          | Per Protocol Set                                      |
| PT           | Preferred Term                                        |
| RBC          | Red Blood Cells                                       |
| SADR         | Serious Adverse Drug Reaction                         |
| SAE          | Serious Adverse Event                                 |
| SAS          | Self-Rating Anxiety Scale                             |
| Scr          | Serum Creatinine                                      |
| SD           | Standard Deviation                                    |
| SDS          | Self-Rating Depression Scale                          |
| SF-36        | Quality of Life Scale                                 |
| SOC          | System Organ Class                                    |
| SS           | Safety Set                                            |
| TBIL         | Total Bilirubin                                       |
| TEAE         | Treatment-Emergent Adverse Event                      |
| VAS          | Visual analog scale                                   |
| WBC          | White Blood Cells                                     |
| WHO          | World Health Organization                             |
| $\gamma$ -GT | Gamma-Glutamyl Transferase                            |

# **Prospective, Randomized, Double-Blind, Multicenter Clinical Study on Danlu Capsule for the Treatment of Mammary Gland Hyperplasia: Statistical Analysis Plan**

## **1 Background**

Breast hyperplasia with breast pain is relatively common among women. Although it is usually associated with mild self-limiting pain, approximately 15% of affected women still require treatment. The current first-line treatment for breast pain is conservative therapy, including physical support, over-the-counter analgesics, and adjustment of hormonal medications used by the patient. When this is ineffective, second-line treatments such as tamoxifen may be recommended, but they can also cause menopausal-like symptoms. Therefore, there is an urgent need to explore safer and more effective treatment options. Danlu Capsule is a traditional Chinese medicine preparation for the treatment of breast hyperplasia. Previous studies have suggested that it has certain therapeutic effects in relieving symptoms of breast hyperplasia, improving breast pain, and reducing the size of breast lumps. However, no prospective randomized controlled double-blind study has been conducted to further clarify the clinical efficacy, safety, and mechanism of action of Danlu Capsule in treating breast pain.

This project focuses on the prominent issue of the lack of a standard and safe treatment for breast hyperplasia with breast pain. It aims to improve the breast pain symptoms of clinical patients by conducting a multicenter prospective randomized double-blind controlled study to clarify the clinical efficacy of Danlu capsule in treating breast hyperplasia with breast pain. This will provide an effective and safe clinical treatment option for patients with breast hyperplasia and breast pain. This statistical analysis plan is developed based on the protocol of the “Prospective Randomized Double-Blind Multicenter Clinical Study of Danlu Capsule for the Treatment of Breast Hyperplasia” (Project Number: WFCMS2024015) and the case report form (CRF version date: February 20, 2025, CRF version number: 1.0). The statistical analysis plan will be finalized before the database lock of this study.

## **2 Objectives**

To evaluate the efficacy and safety of Danlu capsule in the treatment of breast hyperplasia.

## **3 Study Design**

A randomized, double-blind, placebo-controlled, multicenter clinical study design will be adopted, and it is expected to be conducted concurrently at ten research centers across the country.

## **4 Study Medication and Administration**

### **4.1 Study Medications**

- Treatment medication: Danlu capsule; manufacturer: Jiangsu Sino-Pharmaceutical Group Co., Ltd.; specification: 0.5 g per capsule; dosage: 2.0 g per dose, three times per day.
- Placebo medication: Danlu capsule placebo; manufacturer: Jiangsu Sino-Pharmaceutical Group Co., Ltd.; specification: 0.5 g per capsule; dosage: 2.0 g per dose, three times per day.

### **4.2 Treatment Duration**

The treatment period is eight weeks, followed by a one-month follow-up after discontinuation of the medication.

### **4.3 Concomitant Medications**

During the entire treatment period, the use of other Western medicines, traditional Chinese medicines, patent Chinese medicines, or external therapies with similar functions and indications as the study medication is prohibited. If any other non-prohibited Western medicines, traditional Chinese medicines, or patent Chinese medicines have been used, their names, reasons for use, dosage, and duration of treatment should be recorded in detail on the case observation form.

## **5 Efficacy and Safety Assessments**

### **5.1 Efficacy Evaluation**

### 5.1.1 Primary Efficacy Endpoint

Breast pain assessment: The visual analog scale (VAS) will be used to assess the severity of breast pain before and after treatment. The scale ranges from 0 to 10, with 0 indicating no pain and 10 indicating severe pain. Higher scores indicate more severe pain. The primary outcome is defined as the change in the breast pain VAS score from baseline to the 8-week time point.

### 5.1.2 Secondary Efficacy Endpoints

#### (1) Quality of life scale (SF-36)

The SF-36 scale consists of 36 items and evaluates eight dimensions of health-related quality of life: physical functioning, role-physical, bodily pain, general health, vitality, social functioning, role-emotional, and mental health. Assessments will be conducted at baseline and after treatment.

#### (2) Anxiety and depression assessment scales

The patient health questionnaire-9 (PHQ-9), generalized anxiety disorder-7 (GAD-7), self-rating depression scale (SDS), and self-rating anxiety scale (SAS) will be administered at baseline and after pharmacological intervention to assess the levels of anxiety and depression in patients.

#### (3) Breast lump changes

Professional ultrasound physicians will use breast ultrasound and other examinations to measure the size, number, and texture of breast lumps and assess the changes in these lumps before and after treatment.

#### (4) Hormonal regulation indicators

Serum levels of estrogen, progesterone, prolactin, and other hormones will be measured before and after treatment to evaluate hormonal changes.

#### (5) Cytokines

Levels of interleukin-6 (IL-6), tumor necrosis factor-alpha (TNF- $\alpha$ ), and other cytokines will be measured before and after treatment to assess changes.

## 5.2 Safety Evaluation

#### (1) Incidence of adverse events/adverse reactions.

#### (2) Laboratory tests (complete blood count, hepatic and renal function).

## 6 Statistical Analysis Methods

### 6.1 Hypothesis Testing

Null hypothesis  $H_0$ :  $P_1 - P_2 = 0$ ,

Alternative hypothesis  $H_1$ :  $P_1 - P_2 \neq 0$ ,

Where  $P_1$  is the mean of the treatment group and  $P_2$  is the mean of the control group.

### 6.2 Sample Size Estimation

Based on the literature (Jiangsu Journal of Traditional Chinese Medicine, 2021, 53(8): 3 and Journal of Traditional Chinese Medicine, 2019(17): 5), the reduction in breast pain VAS score after two menstrual cycles of treatment with Danlu capsule is 3.2 points, while the reduction in the control group (placebo) is approximately 1.5 points, with a standard deviation of 3.4 points. The sample size for this superiority trial was calculated using a t-test. Based on a superiority margin of 0, a two-sided  $\alpha$  of 0.05, and  $\beta$  of 0.05 (power = 95%), with 1:1 allocation, the required sample size per group was determined to be 105 using PASS 21.0 software. Considering a dropout rate of 20%, the sample size is increased to 132 cases per group, resulting in a total of 264 cases.

### 6.3 Statistical Analysis Data Sets

(1) Full analysis set (FAS): The collection of all cases that were randomized and received at least one dose of the study medication. The primary study conclusions are based on the results of the FAS analysis.

(2) Per-protocol set (PPS): A dataset generated by participants who fully complied with the study protocol. Compliance includes the treatment received, the availability of measurements for the primary endpoint, and no major deviations from the study protocol. The PPS analysis is used for the primary efficacy endpoint.

(3) Safety set (SS): The actual data of participants who received at least one treatment and have post-treatment safety indicator records. The incidence of adverse reactions is calculated using the number of cases in the SS as the denominator.

## **6.4 Content and Methods of Statistical Analysis**

### **6.4.1 General Principles of Statistical Analysis**

(1) Statistical analysis software: SAS 9.4 software will be used for statistical analysis.

(2) Statistical tests: All statistical tests will be two-sided. A p-value less than or equal to 0.05 will be considered to indicate a statistically significant difference.

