#### **Secondary Efficacy Endpoint Analysis:**

(1) Quality of life scale (SF-36) Score Changes at weeks 4, 8, and 12 (one month after discontinuation of treatment):

Group differences will be compared using MMRM, with the model including treatment group, visit, group-by-visit interaction, and baseline value as a covariate. Missing values will not be imputed. The analysis will be based on the actual data in the FAS.

(2) Anxiety and depression assessment scale score changes at weeks 4, 8, and 12 (one month after discontinuation of treatment):

Group differences will be compared using MMRM, with the model including treatment group, visit, group-by-visit interaction, and baseline value as a covariate. Missing values will not be imputed. The analysis will be based on the actual data in the FAS.

(3) Breast lump size changes at weeks 4 and 12 (one month after discontinuation of treatment):

Group differences will be compared using MMRM, with the model including treatment group, visit, group-by-visit interaction, and baseline value as a covariate. Missing values will not be imputed. The analysis will be based on the actual data in the FAS.

(4) Hormonal regulation indicators (serum estrogen, progesterone, prolactin) changes:

Group differences will be compared using the Wilcoxon test. The analysis will be based on the actual data in the FAS.

(5) Cytokine (IL-6, TNF- $\alpha$ ) changes:

Group differences will be compared using the Wilcoxon test. The analysis will be based on the actual data in the FAS.

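### Section 6.4.1 calls any p-value of 0.05 or less significant, and about 47 secondary comparisons are neither ordered, adjusted nor labelled nominal

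*Supplement*

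**What the plan says.** Section 6.4.1(2) covers every test in the plan: "All statistical tests will be two-sided", and then "A p-value less than or equal to 0.05 will be considered to indicate a statistically significant difference". It does not separate primary from secondary comparisons.

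The primary outcome (5.1.1) is a single comparison, the change in breast pain VAS at week 8. Section 6.3 bases the primary conclusions on the FAS.

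The secondary outcomes are broad:
- Section 5.1.2 says "The SF-36 scale consists of 36 items and evaluates eight dimensions of health-related quality of life", and 6.4.6 has these compared at weeks 4, 8 and 12.
- Four mood scales (PHQ-9, GAD-7, SDS, SAS) follow the same pattern: "Anxiety and depression assessment scale score changes at weeks 4, 8, and 12 (one month after discontinuation of treatment".
- Lump measures are compared at two visits.
- Three hormones and two cytokines are each compared once.

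The shells in section 7.4 give each measure its own p-value, at each visit for the repeated measures. The SAP contains no hierarchy, gatekeeping, adjustment or key secondary endpoint. Only section 6.4.4 treats p-values as descriptive, and it covers demographic and baseline data alone.

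**The concern.** A rule that labels every small p-value significant, applied to several dozen unranked comparisons, will on average produce some significant results by chance. Here they would be effects on quality of life, mood, lumps, hormones or cytokines, and section 1 says that efficacy and mechanism of action still need to be clarified. Because the plan gives these results the same label as the primary result, a reader of the final report could not tell from the label which findings had controlled error. Section 6.4.4 shows that the authors had a way to mark p-values as descriptive. They did not use it for the secondary outcomes.

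**Working it through.** **The plan's own calculation.** Section 6.2 takes a VAS reduction of 3.2 points on drug and 1.5 on placebo (difference 1.7), SD 3.4, two-sided alpha 0.05, and a beta "of 0.05 (power = 95%), with 1:1 allocation".
- Normal approximation: n = 2 × (1.960 + 1.645)² × (3.4/1.7)² = 2 × 13.0 × 4 ≈ 104 per group.
- Noncentral t: power is 0.9483 at 104 and 0.9501 at 105, so 105 per group, as stated.
- Dropout: 105/0.80 = 131.25, so 132 per group, as stated.

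The sizing is sound and concerns one comparison only.

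**Count of secondary between-group p-values.**

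| Group | Shells | Count |
|---|---|---|
| SF-36 | Tables 4-8 to 4-15 | 8 × 3 = 24 |
| Mood scales | Tables 4-16 to 4-19 | 4 × 3 = 12 |
| Lump (diameter, size score, consistency score) | Tables 4-5 to 4-7 | 3 × 2 = 6 |
| Hormones | Tables 4-20 to 4-22 | 3 |
| Cytokines | Tables 4-23, 4-24 | 2 |
| Total | | 47 |

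There are two qualifications. The body of Table 4-14 (role-emotional) is not shown, so its three p-values are inferred from 6.4.6. Section 6.4.6 itself names only lump size, at two visits; counted that way the total is 47 − 4 = 43. The text gives weeks 4 and 12 for the lump and the shells give weeks 8 and 12. That is a separate inconsistency and does not change the count.

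The VAS MMRM p-values (three visits in each of FAS and PPS) and the seven safety p-values in Table 5-1 fall under the same rule but are outside the 47.

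**Expected number of chance results with no effect on any secondary outcome.** 47 × 0.05 = 2.35 (43 × 0.05 = 2.15). This holds under any correlation. By symmetry half of these, 1.175, would favour the drug.

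**Chance of at least one, if independent.**
- Either direction: 1 − 0.95^47 = 0.910 (0.890 with 43 tests).
- Favouring the drug: 1 − 0.975^47 = 0.696.

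**Chance of at least one, if correlated.** The SAP gives no correlations, so these are assumptions. Each row comes from 200,000 simulated sets of 47 z-statistics. In the block rows the three values are the correlations for the same measure at two visits, for different measures within the SF-36, mood or lump group, and for SF-36 with mood. Pairs at different visits are further multiplied by the first value, and all other pairs are taken as uncorrelated.

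| Assumed correlation | Either direction | Favouring the drug |
|---|---|---|
| Block 0.5 / 0.3 / 0.2 | 0.85 | 0.56 |
| Block 0.5 / 0.5 / 0.4 | 0.79 | 0.50 |
| Block 0.7 / 0.5 / 0.4 | 0.76 | 0.46 |
| Block 0.7 / 0.7 / 0.6 | 0.66 | 0.39 |
| Block 0.8 / 0.7 / 0.6 | 0.63 | 0.37 |
| Block 0.9 / 0.8 / 0.7 | 0.54 | 0.31 |
| Common 0.5, all 47 | 0.61 | 0.31 |
| Common 0.7, all 47 | 0.40 | 0.20 |

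Of these rows, only the last falls below one half in either direction. It requires hormones and cytokines to be as strongly tied to questionnaire scores as the scores are to each other. A higher common correlation would lower the figure further.

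**The case against.** The confirmatory structure is already singular: one primary outcome at one visit, one pair of hypotheses, a sample size built on VAS alone, and no interim analysis. Unadjusted secondary tests beside one primary endpoint are common, and many readers treat them as supportive. This stands, and it is why the point concerns how secondary results are labelled rather than the validity of the primary test.

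A reader might infer more than the documents support:
- **That the trial's main error rate is inflated.** It is not; secondary tests do not affect the primary comparison.
- **That a false claim of benefit is more likely than not.** This holds under independence (70%), but most of the correlated scenarios put it below one half. The larger figures count chance results in either direction, including those against the drug.
- **That the sponsor intends to claim secondary effects even if the primary fails.** No passage says so. The rule merely does not prevent it.

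The 91% figure assumes independence among repeated visits on the same patients and among overlapping scales such as PHQ-9 with SDS. That is implausible, so it marks the upper end of the range.

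The protocol is not shown and might rank the secondary endpoints, so the absence of a named key secondary endpoint carries less weight. But the significance rule is the SAP's own, and it is written for all tests.

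**Conclusion.** The point holds as a fault in a stated rule. Followed as written, section 6.4.1(2) would label about 2.35 of 47 secondary comparisons significant on average if the drug had no effect on any of them. The chance of at least one in either direction is 91% under independence, about 54% to 85% under the block correlations assumed, and about 40% at a common correlation of 0.7. For a false result favouring the drug, it is 70% under independence and about 20% to 56% across the correlated scenarios. Apart from the independence figures, these probabilities rest on assumed correlations; the expected count does not. Using 43 tests instead of 47 leaves the conclusion unchanged. This should be corrected, but it does not threaten the primary analysis.

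**What to change.** Before unblinding, and within the SAP's own timetable of finalisation before database lock:

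- Reword 6.4.1(2) so that a finding of statistical significance applies only to the primary comparison, the week-8 VAS ANCOVA in the FAS.
- State that all other p-values are nominal and support no confirmatory claim.
- Add 95% confidence intervals for the between-group differences in Tables 4-20 to 4-24. Those shells give a median and IQR for the difference, whereas the MMRM shells that are shown already carry intervals.
- If the sponsor wants a secondary claim, name a short fixed sequence of week-8 endpoints, each tested at 0.05 only after the primary and every earlier step succeed. If a lump measure is included, reconcile its visits first.

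The cost is a few sentences and five amended shells, with no change to the sample size or the primary analysis. The downside is that fewer secondary results may be called significant.

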### **6.4.2 Handling of Missing Values**

For missing values of primary outcomes in efficacy analyses: the last observation carried forward method will be adopted for imputation in the primary analysis, and multiple imputation will be used for the missing primary outcome data as a sensitivity analysis to verify result robustness.

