### **6.4.6 Efficacy Analysis**

#### **Primary Efficacy Endpoint Analysis:**

The difference between the breast pain VAS score at eight week and the baseline value will be analyzed using Analysis of Covariance (ANCOVA), with treatment group and center as fixed effects, and baseline value as a covariate. Missing values will be imputed using the LOCF method. Both PPS and FAS analyses will be conducted. Changes in breast pain VAS score from baseline at weeks 4, 8, and 12 (1 month after discontinuation of treatment) will be compared between groups using mixed-effects model for repeated measures (MMRM), with the model including treatment group, visit, group-by-visit interaction, and baseline value as a covariate. Missing values will not be imputed.

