### 7.4 Efficacy Analysis

#### 7.4.1 Breast Pain Analysis

Table 4-1 Analysis of covariance (ANCOVA) of change in breast pain score at week 8 (full analysis set, FAS)

Table 4-2 Analysis of covariance (ANCOVA) of change in breast pain score at week 8 (per protocol set, PPS)

| Visit                       | Treatment group (N=XXX) | Placebo group (N=XXX) |
|-----------------------------|-------------------------|-----------------------|
| Baseline                    |                         |                       |
| N (NMissing)                | XXX                     | XXX                   |
| Mean $\pm$ SD               | XX.XX $\pm$ XX.XX       | XX.XX $\pm$ XX.XX     |
| 8 week                      |                         |                       |
| N (NMissing)                | XXX                     | XXX                   |
| Mean $\pm$ SD               | XX.XX $\pm$ XX.XX       | XX.XX $\pm$ XX.XX     |
| Change from baseline        |                         |                       |
| N (NMissing)                | XXX                     | XXX                   |
| Mean $\pm$ SD               | XX.XX $\pm$ XX.XX       | XX.XX $\pm$ XX.XX     |
| LS mean (SE)                | XX.XX (XX.XX)           | XX.XX (XX.XX)         |
| LS mean difference (95% CI) | XX.XX (XX.XX, XX.XX)    |                       |
| P-value                     | XX.XX                   |                       |

Note: Analysis of covariance (ANCOVA) was used, with treatment group and center as fixed effects, and baseline value as a covariate. Missing values were imputed using the last observation carried forward (LOCF) method.

Table 4-3 Temporal comparison of between-group differences in LSMEANS of change in breast pain score by

MMRM (full analysis set, FAS)

Table 4-4 Temporal comparison of between-group differences in LSMEANS of change in breast pain score by MMRM (per protocol set, PPS)

|                             | Treatment group (N=XXX) | Placebo group (N=XXX) |
|-----------------------------|-------------------------|-----------------------|
| Baseline                    |                         |                       |
| N (NMissing)                | XXX                     | XXX                   |
| Mean±SD                     | XX.XX±XX.XX             | XX.XX±XX.XX           |
| 4 week                      |                         |                       |
| N (NMissing)                | XXX                     | XXX                   |

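### The deciding week-8 pain analysis fills missing scores by LOCF, which biases the treatment contrast, while an MMRM without imputation is already planned and could decide instead

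*Supplement*

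**What the plan says.** - **Endpoint.** SAP section 5.1.1: "The primary outcome is defined as the change in the breast pain VAS score from baseline to the 8-week time point".
- **Missing-data rule.** Section 6.4.2, for missing primary outcomes: "the last observation carried forward method will be adopted for imputation in the primary analysis".
- **Deciding analysis.** Section 6.4.6 specifies an ANCOVA with treatment group, center and baseline, and adds: "Missing values will be imputed using the LOCF method". The note to Tables 4-1 and 4-2 (section 7.4.1) repeats this: "Missing values were imputed using the last observation carried forward (LOCF) method".
- **Deciding population.** Section 6.3: "The primary study conclusions are based on the results of the FAS analysis". The FAS is defined as "The collection of all cases that were randomized and received at least one dose of the study medication", so no post-baseline pain score is required.
- **Expected dropout.** Section 6.2: "Considering a dropout rate of 20%, the sample size is increased to 132 cases per group". This is one allowance, not split by arm.
- **Sensitivity analysis.** Section 6.4.2: "multiple imputation will be used for the missing primary outcome data as a sensitivity analysis to verify result robustness". No imputation model or missing-data assumption is given.
- **Additional analysis.** Section 6.4.6 plans an MMRM of the VAS change at weeks 4, 8 and 12 without imputation. Tables 4-3 and 4-4 report its week-8 contrast for the FAS and the PPS.

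The SAP gives no reason for choosing LOCF. It does not say what LOCF does for a participant with no post-baseline VAS.

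**The concern.** LOCF stands in for a week-8 score only if pain stops changing at the last visit attended. The plan's own planning figures have pain falling in both arms, by different amounts. The LOCF contrast therefore mixes the week-8 effect with how many participants leave each arm and when. Equal dropout shrinks the effect. Unequal dropout can hide an effect, exaggerate it, or produce one where there is none; more dropout on placebo favours the drug. Single imputation also treats filled-in values as observed, so the confidence interval ignores imputation uncertainty.

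The PPS requires an available primary measurement, so LOCF matters mainly in the FAS, which is the set that decides. An analysis of the same outcome that does not need this assumption is already in the plan, but in a supporting role.

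**Working it through.** **1. The plan's own figure.** Difference 3.2 − 1.5 = 1.7, SD 3.4, two-sided alpha 0.05, power 95%. The normal approximation gives 2 × (1.960 + 1.645)² × 3.4² / 1.7² = 103.96, so 104 per group. The exact t-test gives 105 (power 0.9501 at 105, 0.9483 at 104). Then 105 / 0.8 = 131.25, so 132. Section 6.2 is reproduced.

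**2. Assumptions not in the documents.** Dropout is random within arm. *d* is the dropout proportion in an arm. *g* is the share of dropouts who have a week-4 score (0, 0.5 or 1); the others have baseline carried, which means zero change. *f* is week-4 improvement as a fraction of week-8 improvement (0.50 or 0.75). Arm splits of 15/25, 10/30 and 30/10 (drug/placebo) all average the planned 20%.

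**3. Formulas.** With true week-8 improvement *m* and s = 3.4, each arm under LOCF has

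- mean μ = m[(1 − d) + d·g·f]
- variance V = (1 − d)(s² + m²) + d·g(s² + (f·m)²) − μ²

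The contrast is Δ = μ(drug) − μ(placebo), with SE = √[(V(drug) + V(placebo))/132]. The rejection rate is Φ(|Δ|/SE − 1.96) + Φ(−|Δ|/SE − 1.96).

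**4. One case in full** (20/20, g = 0). Δ = 0.8 × 3.2 − 0.8 × 1.5 = 2.56 − 1.20 = 1.36. V(drug) = 0.8 × (11.56 + 10.24) − 2.56² = 10.886. V(placebo) = 0.8 × (11.56 + 2.25) − 1.20² = 9.608. SE = √(20.494/132) = 0.394. Power = Φ(1.36/0.394 − 1.96) = Φ(1.49) = 93%.

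**5. All cases** (Δ, rejection rate):

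| Dropout drug/placebo; true improvement drug/placebo | g = 0 | g = 0.5, f = 0.50 | g = 1, f = 0.50 | g = 1, f = 0.75 |
|---|---|---|---|---|
| 20/20; 3.2/1.5 | 1.36, 93% | 1.45, 94% | 1.53, 95% | 1.62, 97% |
| 30/10; 3.2/1.5 | 0.89, 61% | 1.09, 76% | 1.30, 86% | 1.50, 95% |
| 10/30; 3.2/1.5 | 1.83, >99% | 1.80, 99% | 1.77, 99% | 1.73, 99% |
| 20/20; 1.5/1.5 (no effect) | 0, 5% | 0, 5% | 0, 5% | 0, 5% |
| 15/25; 1.5/1.5 (no effect) | 0.15, 7% | 0.11, 6% | 0.08, 5% | 0.04, 5% |
| 10/30; 1.5/1.5 (no effect) | 0.30, 12% | 0.23, 9% | 0.15, 6% | 0.08, 5% |
| 10/30; 3.2/3.2 (no effect) | 0.64, 35% | 0.48, 21% | 0.32, 12% | 0.16, 7% |

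**6. Check by simulation.** 5,000 runs per scenario, ANCOVA with baseline and no center term, correlation 0.6 between week-4 and week-8 change. LOCF gave power of 93-95% for 20/20 with f = 0.50, and 75% for 30/10 in the middle case. With no drug effect it rejected in 5.3% of runs (20/20; both arms improving 1.5). For 10/30 it rejected in 8.6% and 11.8% (both improving 1.5) and in 20.6% and 34.1% (both improving 3.2), each for g = 0.5 and g = 0. Under the same dropout, ANCOVA on observed week-8 scores gave about 1.70, power about 95% and type I error of 4.6-5.5%. A separate simulation (4,000 runs, g = 0.5, f = 0.50) of a likelihood estimate from weeks 4 and 8, the principle behind the MMRM, gave 1.70 with 96% power for 20/20 and 30/10, and 5% type I error for 15/25 and 10/30.

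**The case against.** Several points on the other side are fair.

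- **Type I error.** A reader might infer that LOCF with 20% dropout inflates the false-positive rate as such. The documents do not support that. Section 6.2 has one allowance for both arms and nothing predicts imbalance. With equal random dropout the test is nominal and LOCF only costs effect size.
- **The largest error rates.** The 21-35% figures suppose that both arms improve 3.2 points under the null. The plan's placebo figure is 1.5, which gives 9-12%.
- **Baseline carried forward.** A reader might take it as planned that anyone leaving before week 4 is scored as zero change. The SAP does not say so. The FAS admits such participants and the LOCF rule is silent on them. If every dropout has a week-4 score, the 10/30 error rates fall to 5-6% (improvement 1.5) and 7-12% (improvement 3.2).
- **Week-4 response.** The documents give none; 50-75% is assumed, and a higher fraction shrinks the bias.
- **Planned checks.** Multiple imputation and the MMRM are prespecified, so a result driven by LOCF would probably be noticed.
- **The MMRM as planned.** It omits center and names no covariance structure. It is valid under missing at random, not under every mechanism. Multiple imputation could also serve as the primary analysis.

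These points limit the size of the problem but do not remove it. The sensitivity analysis has no stated model, the SAP does not say what follows if it disagrees, and the FAS LOCF result still decides. Dropout by arm cannot be known in advance, which is a reason not to let the deciding estimate depend on it.

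**Conclusion.** The concern holds in a limited form. LOCF in the deciding FAS analysis biases the week-8 contrast whenever pain is still changing, as the planning figures suggest.

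- **Equal 20% dropout:** 1.70 becomes about 1.36-1.62, a loss of 5-20%. Power stays at about 93% or more, with nominal type I error.
- **30% drug, 10% placebo:** about 0.89-1.50, with power down to about 61% at worst.
- **10% drug, 30% placebo, no drug effect:** type I error of about 9-12% if both arms improve 1.5 points, and about 21-35% if both improve 3.2. These ranges take week-4 improvement as half of week-8 improvement and baseline carried for half to all dropouts; under milder assumptions the error moves back towards 5%.

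All figures assume random dropout within arm. The 20% is a planning allowance, so the actual bias depends on the realised number, timing and balance of dropouts.

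**What to change.** In sections 6.4.2 and 6.4.6 and in the note to Table 4-1:

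1. Make the FAS week-8 treatment contrast from the planned MMRM the primary analysis. Add center to the model and state the covariance structure.
2. Move ANCOVA with LOCF to a supportive analysis, and state how it treats participants with no post-baseline VAS.
3. Keep multiple imputation as the sensitivity analysis and specify its model. Preferably make it delta-adjusted or reference-based, so that it tests departures from missing at random.

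Cost: SAP wording, a change in the order of tables already planned, and a little imputation code, all before unblinding. The Background section says the SAP is finalized before database lock. No extra data or participants are needed. Downside: participants with no post-baseline VAS would contribute only through the imputation analysis.
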